#### Screening and recruitment of patients

Patient recruitment is widely regarded as the most challenging aspect of conducting both individual-patient and cluster RCTs [49]. Failure to recruit target sample sizes can lead to costly and lengthy extensions and loss of power. In primary care, time constraints, GPs forgetting to recruit, and identification of too few eligible patients threaten recruitment rates [50]. Furthermore, cluster trials in health settings are at high risk of selection bias because of selective recruitment of patients by professionals who are aware of intervention allocation [51], and through systematic differences in referral behavior between the clusters in each arm [34].

To ensure adequate recruitment of patients and to minimize the risk of selection bias, we will recruit patients by case-finding of eligible patients with depression and CHD/diabetes rather than relying on direct GP referral. Such reliance in mental-health trials has proven to be too slow and inefficient [52], and recent individual-patient and cluster trials of collaborative care in the UK and USA have shown that screening eligible patients for depression is an efficient and acceptable way to improve recruitment rates. Accordingly, in partnership with the NIHR Mental Health Research Network (MHRN), the practice staff will work with clinical studies officers (CSOs) to compile a mailing database of all patients on the diabetes/CHD registers held in each participating general practice. GPs in participating practices will then be paid to review this database to exclude patients that do not meet the trial inclusion criteria and to remove recently deceased patients. CSOs will then assign study identification numbers to each patient on the mailing database, and in partnership with the CLAHRC team, will send a study pack to all eligible patients on the database, including a study invitation letter, an information sheet, a consent form, and a request for translation. Reminder letters and replacement study packs will be sent 3 weeks later to patients who have not responded to the initial mailing. Because mail-based recruitment is known to yield poor returns, non-responders to the reminder letter will also be telephoned by CSOs [53]. Non-responders of South Asian origin and those do not speak English will be telephoned by a member of the COINCIDE study team proficient in Bengali, Gujarati, and Urdu, who is blinded to intervention allocation.

After receipt of consent forms, CLAHRC research staff blinded to the intervention allocation will make an initial screening appointment with eligible patients. Screening will be undertaken over the telephone using the PHQ-9. Patients who score greater than or equal to 10 on the PHQ-9 will be informed that they provisionally meet the inclusion criteria for entry into the trial; patients who score less than this will be informed that they are not eligible for the study.

Scores greater than or equal to 10 on the PHQ-9 are indicative of major depression [48]. Although using a more conservative cut-off of greater than or equal to 12 might improve the accuracy of predicting major depression with the PHQ-9 [54], using the lower cut-off of 10 has two advantages. First, we will be able to make comparisons with international studies that have used similar thresholds for depression. Second, using the lower cut-off of greater than or equal to 10 allows detection of sub-threshold depression or ‘diabetes -elated distress’, which has been identified as a key mediating factor between depression and glycemic control in diabetes [55]. It could be argued that such levels of distress should be recognized earlier and managed in people with diabetes.

Administration of the PHQ-9 in person or by telephone produce similar results, making telephone assessments a reliable screening method for depression in primary care [56]. Furthermore, the case-finding ability of the PHQ-9 is comparable with that of standardized diagnostic clinical interviews when used in medical settings [57], and is as good as, if not superior to, the Hospital Anxiety and Depression Scale when used to screen for depression in non-psychiatric populations [58].

Remission is common for mild to moderate depression, and the ability of this trial to detect treatment effects will be improved if the sample includes only patients with persistent depressive symptoms. To exclude patients with transient and spontaneously remitting depression research staff blinded to the intervention allocation will therefore visit patients who scored greater than or equal to 10 on the initial telephone PHQ-9 screen to undertake a second PHQ-9 screen. Patients who score greater than or equal to 10 at this second PHQ screening appointment will then be invited to complete baseline assessments and enter the trial. The researcher will tell the participant’s GP about their involvement in the study. Patients who score less than or equal to 9 at this second screening appointment will be informed that they do not meet the study inclusion criteria and will be excluded; their GP will be informed by the research team that they will take no further part in the study at this stage. A CONSORT flow diagram of the recruitment and screening strategy is shown in Figure 1.

Researchers blinded to the intervention allocation will forward the details of those patients who are eligible to join the trial (those who scored ≥10 on PHQ-9 at the second screening appointment) to the COINCIDE trial manager. The trial manager will enter these details onto a password-protected and encrypted database. Within 3 working days of the second screening appointment, the trial manager will contact the clinical lead of the IAPT team to pass on contact details of patients in the collaborative-care arm who have met the inclusion criteria. PWPs will then contact the patient directly to set up a first appointment.

### Intervention design

#### Collaborative care

PWPs will case-manage people with diabetes and/or CHD and depression in partnership with the patient’s GP and a practice nurse. Each patient will receive up to eight sessions with the PWP over 12 weeks. Sessions can be conducted in person or by telephone, depending on patient preference. The first session will be 45 to 60 minutes long, during which the case manager will complete a detailed biopsychosocial patient assessment; elicit the patient’s ABC-E (autonomic, behavior, cognition, environment)) model about diabetes and/or CHD and links with low mood; briefly educate the patient about diabetes/CHD and depression; assess risk; and introduce the treatment manual and develop with the patient a main problem statement. All other sessions will be between 30 and 40 minutes in length. During the second session, patients will select which intervention they prefer, and active treatment will start during the third session. Although outcomes in depression scores are the main focus of this study, treatment manuals have been designed to incorporate interventions that address any symptoms of anxiety that may present alongside depression. This assessment and treatment schedule is consistent with the delivery of brief psychological therapies in the NHS, where six to eight sessions is a common treatment length.

A 10 minute collaborative meeting (by telephone or in person) between the patient and the case manager and a practice nurse will take place at the end of the second and eighth sessions. These collaborative meetings will focus on reviewing patients’ progress with their main problem statement and goals, reviewing relevant health outcomes (for example, HbA1_c_, lipids), and a medication review. The collaborative meeting at the end of the eighth session also includes opportunities for the collaborative-care team to discuss with the patient the next steps to be taken, either to maintain health gains or, if the patient’s mood has not improved, to review medication (for example, change anti-depressant or increase dose) or referral to higher-intensity interventions. The rationale for these collaborative meetings is to embed collaborative ways of working into the care of patients with diabetes/CHD beyond the initial 3-month treatment phase, especially in relation to goal-setting and action planning.

The key principles of the intervention are that it is patient centered and includes partnership working, proactive follow-up, and integrated communication and care between the patient, a mental-health professional (PWP), and a GP and/or a practice nurse. The type of psychological intervention used will be chosen by the patient and will be goal-orientated to primarily improve mental heath outcomes. However, the delivery of depression treatments in this population might also support the management of patients’ physical health, for example, by giving lifestyle advice about diet and exercise. In this sense, the COINCIDE trial aims to use collaborative care as a platform to integrate physical and mental health care for people with depression and diabetes and/or CHD.

#### Usual care

Patients allocated to the control group will receive their usual care by their primary-care team. For patients with diabetes and CHD, usual care includes meeting QOF clinical indicators as part of the General Medical Services and Personal Medical Services [47]. Because this is a pragmatic trial, patients in the usual care group will still be eligible to receive anti-depressant treatment and referral for psychological therapy. However, if patients in the usual care group are referred to an IAPT team for psychological therapy they will not receive treatment from a PWP who has been trained in LTCs as part of the COINCIDE trial. It is not yet known if collaborative care delivered in the UK NHS as part of a low-intensity (or step 2) intervention is any more effective than standard care for depression in people with LTCs. In this sense, patients in the usual care group with recognized depression are not disadvantaged, as they will still have access to evidence-based treatments.

Additionally, we do not anticipate that participation in the trial will radically alter care pathways for depression in the control group. There is solid evidence that case-finding or screening for depression does not in itself lead to improvements in detection and management of depression by clinicians [59], nor is case-finding for depression known to be a necessary component of effective collaborative care interventions for depression. When used as a mechanism to increase recruitment in a clinical trial, screening alone is unlikely to affect the quality of care available to patients with recognized depression, thus preserving the comparison in the trial between collaborative care and usual care for depression. We will record all aspects of the patients’ usual care in the control group, and the follow-up assessments will be identical to those used in the intervention group.

#### Stepped-care algorithm and risk management

An adapted stepped-care approach will be used based on NICE recommendations for treating depression [9,10]. Where demand exceeds supply, stepped-care models potentially offer a framework to organize and provide services in the most efficient and effective way by supporting patients, carers, and practitioners in identifying and accessing the least restrictive (and least intensive) but most effective intervention first [20]. If a patient does not benefit from the intervention initially offered, or declines an intervention, they should be offered an appropriate intervention from the next step. In theory, the stepped-care model should be self-correcting, because patients can be stepped up when they are not progressing to agreed targets. Currently, collaborative care is recommended as a step 3 or high-intensity intervention for depression in cases where the patient also has a LTC and associated functional impairments. However, in keeping with previous studies of collaborative care [25], the COINCIDE trial defines collaborative care as a health-services intervention to improve the quality and choice of evidence-based care for depression, rather than as a therapeutic intervention in itself. In this sense, collaborative care is an organizational framework that can facilitate and improve the delivery of all types of therapeutic interventions.

Following formal review after the fourth and eighth sessions, if patients have persistent depressive symptoms (<50% decrease in severity on PHQ-9) then PWPs, in partnership with the patient and in consultation with their clinical supervisor, will discuss the most appropriate action(s) from a range of options: 1) change low-intensity psychological intervention; 2) if patient is not on antidepressants, ask patient to see GP to discuss this option; 3) if patient is already on antidepressants then ask patient to see GP to discuss increase in dose or change of anti-depressant medication; 4) step up to a higher-intensity intervention (which will usually be cognitive and behavioral therapy; CBT). Weekly monitoring between the second and eighth session using tools from the IAPT minimum dataset will support PWPs in reviewing the patients’ progress and implementing the stepped-care algorithm. The local collaborative team (PWPs, supervisors, and GPs) will be able to consult the trial clinical team (LG, KL, [name]) about starting, or adjusting dose, or changing anti-depressant medication, as we recognize that specific medication expertise may not be available within the IAPT team.

Where there is concern about risk of self-harm, suicide, neglect, or harm to others, patients will be stepped up to community mental-health services for assessment and management. This decision will be made in collaboration with the local supervisor, with additional support from the trial clinical team (LG, KL, [name]) where required.

### Intervention components

#### Guided self-help

The treatment, partly delivered with the aid of a patient manual and workbook, is based on an individual-guided self-help program for people with depression and diabetes/CHD delivered by PWPs in collaboration with a GP and practice nurse. Guided self-help based on the principles of CBT is one of a range of low-intensity psychological interventions recommended by NICE [9,10] for people with persistent sub-threshold depressive symptoms and mild to moderate depression and should include the provision of written materials of an appropriate reading age (or alternative media to support access); be supported by a trained practitioner, who typically facilitates the self-help program and reviews progress and outcome; and consist of up to six to eight sessions (in person or by telephone), normally taking place over 9 to 12 weeks, including follow-up.

In the COINCIDE trial, patients in the collaborative-care arm will be offered a choice of brief psychological interventions: behavioral activation (BA), graded exposure, cognitive restructuring, and/or lifestyle changes. Medication management will also be used to ensure that patients have the necessary knowledge to make an informed choice about whether to start an anti-depressant.

#### Behavioral activation

BA is premised on the notion that depression is functional, whereby depressive feelings and thoughts stimulate avoidant behavior, leading to negative reinforcement and a reduction in positive reinforcement and in normal (routine, pleasurable, and necessary) activities. This behavioral model of depression acknowledges that the experience of being depressed includes bi-directional relationships between life events and modified reinforcement schedules and secondary problems such as avoidant coping. The format adopted in this trial is a four-step BA plan to support patients to reschedule activities to reintroduce positive reinforcement, improve thoughts and mood, and reduce avoidant behaviors. In partnership with PWPs, patients will draw up and self-monitor activity schedules, and identify goal-oriented behaviors likely to reinforce anti-depressant environmental contingencies.

BA is as effective and acceptable as higher-intensity CBT for the treatment of depression [60]. Moreover, because it adopts a more parsimonious therapeutic approach than CBT, it can potentially be delivered by low-intensity therapists (such as PWPs), leading to opportunities for implementation in routine settings [61].

#### Graded exposure

The initial stages of the intervention involve the PWPs educating patients about the effects of avoidance and the role of safety behaviors in the maintenance of anxiety, which can in turn lead to withdrawal and depression. Using the patient’s individual symptoms, cognitions and behaviors, the PWPs illustrate how vicious circles (symptom → catastrophic thought → fear → avoidance → disability → symptom) maintain the problem.

Patients are then supported in session to draw up a graded hierarchy of fear-eliciting situations. These take the form of a series of behavioral experiments, carried out between sessions, during which irrational expectations are challenged. Patients are encouraged to work up the hierarchy, remaining in these fearful situations until anxiety has significantly decreased. This process must be completed several times until minimal anxiety is experienced before the patient proceeds to the next step on their hierarchy. A successful exposure intervention results in a reduction in the anxiety response and increased behavioral tolerance of identified triggers. In cases where the PWP identifies specific anxious cognitions within the maintenance cycle that are resistant to exposure, the patient will be helped to consider the evidence for and against these fears and, where appropriate, carry out behavioral experiments between sessions, during which anxious predictions are examined and reflected upon. The successful addition of this intervention should result in a cognitive shift, whereby the patient no longer negatively misinterprets physical symptoms and no longer engages in avoidance or unhelpful safety behaviors. Where anxiety symptoms are longstanding, or complex or specific phobias directly affect self-management, PWPs will facilitate stepping up to high-intensity CBT.

#### Cognitive restructuring

Cognitive restructuring is used to identify and challenge seemingly rational and believable negative thoughts by reframing them as more accurate and realistic beliefs. In COINCIDE, patients will use thought diaries and engage in behavioral experiments to identify situations that trigger negative, often automatic, thought processes, and will work with the PWP to challenge these negative thoughts with more positive and goal-oriented ones.

#### Lifestyle advice

PWPs will work with patients to help them identify and implement lifestyle changes to lead a healthier lifestyle, including addressing sleep habits, diet, exercise, and relaxation.

#### Medication management

PWPs will work with the patient to assess whether they are taking medication as prescribed, address any worries and concerns about the medication and side-effects, provide good-quality information about medication to address concerns, and help to arrange a review of medication with the GP if this is indicated because of patient and/or therapist concerns about side-effects and/or failure to improve.

### Training and supervision

#### Training and supervision of case managers

Case-management training will be delivered by a multidisciplinary team of high-intensity and low-intensity therapists, academic GPs, and consultant psychiatrists, along with disease specialists in diabetes and CHD. PWPs will receive an initial 1-week (5-day) training course that includes classroom sessions and interactive skills practice, along with video demonstrations of conducting a biopsychosocial patient assessment, formulating a shared problem statement, and the collaborative team meeting. PWPs will use a training manual during the training week (Table 1).

**Table 1 T1:** Description and aims of the training

**Day**	**Section**	**Aim**
1	Introduction to collaborative care and LTCs – an overview of the evidence base	Understanding diabetes and CHD
2	Patient-centered interviewing and promoting change	Developing shared problem statements and goal-setting
3	Introduction to psychological interventions for depression and LTCs	Medication management and lifestyle interventions
4	Delivering behavioral activation and cognitive restructuring for depression and LTCs	
5	Maintaining health, effective liaison, supervision and monitoring	

Case managers will receive 1 hour of individual supervision on a weekly basis from a senior mental-health practitioner within their IAPT team; this may be undertaken in person or by telephone, depending on case manager and supervisor preference and availability. This supervision will be structured in accordance with the IAPT PWP case-management supervision guidelines [62,63]. Using this approach, at each session new cases, cases with risk, those not improving by the eighth session and those with missed sessions (did not attend; DNA) are routinely discussed; in addition, every case is reviewed every 4 weeks. The case manager will report the case and include the problem statement, questionnaire scores (PHQ-9; Generalized Anxiety Disorder Assessment-7 [GAD-7]) and risk issues, medication, goals and treatment plan, with the addition of items that specifically focus on the patient’s LTC: the effect of their depression on their physical health and self-management, treatment concordance, progress with diabetes and/or CHD outcomes (for example, hemoglobin A1_c_, lipids), and any additional case-management issues. In addition, case managers will have fortnightly access to the equivalent of 1 hour of clinical skills supervision, conducted in groups and facilitated by a senior mental-health practitioner within their IAPT team, allowing the opportunity for in-depth discussion and further skill development arising from specific cases.

PWPs will keep and maintain notes for the patients they treat using the GP practice computer systems, if this is acceptable to GPs and practice managers. In addition, as part of reporting for the trial, PWPs will keep a monitoring sheet for each patient. This monitoring sheet reports how many sessions patients attended on average, the delivery mode in which they received follow-up (in person or by telephone), and what interventions patients selected.

#### Train the trainer sessions

After completion of follow-ups, irrespective of outcome, the COINCIDE training team will offer training in the collaborative-care model to previously untrained supervisors and clinical leads from IAPT teams enrolled in the trial. These ‘train the trainer’ sessions will be given so that IAPT teams can draw on local expertise to train and then supervise additional step 2 PWPs in using collaborative care for treating depression and diabetes/CHD. This approach will support IAPT teams to build capacity to meet demand for low-intensity psychological interventions from people with diabetes/CHD. This strategy also partly meets IAPT objectives to roll out psychological therapy services to people with LTCs [44], and is consistent with the GM CLAHRCs commitment to support implementation of research into practice.

#### Training workshop for practice nurses

A separate half-day workshop will be run for practice nurses drawn from GP practices randomized to the collaborative-care group. This workshop will be shared with PWPs trained in the collaborative-care model and will focus on delivering integrated care and effective consultation liaison.

### Outcome assessment

#### Primary outcome

The mental-health needs of people with LTCs have historically been under-recognized and under-served in primary care, and the main aim of this trial is to improve the access to and quality of depression care for people with two exemplar LTCs: diabetes and/or CHD. The interventions used are designed primarily to improve depression rather than both depression and physical health outcomes. The primary outcome in this trial is therefore change in depressive symptoms. However, using low-intensity psychological interventions, including lifestyle counseling, to treat depression may also be beneficial for diabetes/CHD, leading to opportunities for therapeutic synergies across multiple conditions. Accordingly, we will also test the effects of collaborative-care interventions on a range of secondary outcomes related to diabetes and CHD and self-care.

The 90-item Symptoms Checklist (SCL-90) depression scale will be used to assess changes in severity of depressive symptoms at 6-months [64]. Response to treatment is defined as greater than or equal to 40% reduction in SCL-90 scores [65]. We will also use the PHQ-9 at baseline and follow-up to measure changes in dichotomous diagnosis of depression [48].

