### Patient recruitment

#### Sample size

Based on a UK trial of collaborative care for major depressive disorder [29] we have powered this trial to detect a standardized effect size of 0.4. If each of the 30 practices (15 in each arm) recruits 15 patients at baseline (450 in total), the study will have > 80% (81.2%) power to detect this size of effect at the 5% level of significance, allowing for an intraclass correlation coefficient (ICC) of 0.06 (that was identified in a previous Phase II trial of collaborative care) and a 20% attrition rate.

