Sensitivity analysis will be used to test the effects of assumptions and data on the ICER, and results of the cost-effectiveness acceptability analysis. These will include testing the effects of varying the discount rate used, extrapolating the results over longer timeframes, the unit cost sets used to value resources, the methods used to impute missing data; and the outcome measure used in the ICER including 1) severity of depressive symptoms (SCL-90, PHQ-9), 2) health perceptions (IPQ), 3) self-management behaviors, and 4) other measures of health status.

SPSS Statistics (IBM, version 20.0) will be used for data manipulation and descriptive analysis. Stata 12 (StataCorp, Texas 77845–4512, USA) will be used for the main statistical analyses, and imputation and estimation of net benefit statistics and cost-effectiveness acceptability analysis [93,94].

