### Analysis

The method of allocation of practices to the collaborative care or control arm will be based on simple randomization (that is, 50:50 chance) for the first six practices. Minimization will be used thereafter with 0.7/0.3 probabilities. For each allocation, the balance score will be estimated based on thresholds for practice list size and deprivation, measured using the Index of Multiple Deprivation.

All analyses will be conducted on an intention-to-treat basis subject to the availability of data. After data cleaning, the preliminary analysis will investigate the pattern of missing baseline and follow-up data. The effect of the collaborative-care treatment program on depression outcomes will be estimated using a multi-level mixed-effects linear regression model, including a random effect for practices, and controlling for the following baseline covariates: patient age, gender, ethnicity, and baseline PHQ-9 score. Given that the continuous outcomes are likely to have a skewed distribution, bootstrap sampling (a method free from parametric assumptions) will be used to derive estimates of error variance for the tests of statistical significance, using 10,000 samples. Sensitivity analysis will be carried out to check the implications of different assumptions about the missing data.

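### Among the effectiveness outcomes the PHQ-9 is used only as a dichotomy, apparently at the entry cut-off of 10; the score already collected would be more precise and easier to interpret

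*Protocol article*

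**What the plan says.** The primary outcome is the SCL-90 depression scale: "depression scale will be used to assess changes in severity of depressive symptoms at 6-months". The same section then gives the PHQ-9 its role: "We will also use the PHQ-9 at baseline and follow-up to measure changes in dichotomous diagnosis of depression". The sentence states no cut-off. The list under Secondary outcomes contains no PHQ-9 severity measure.

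The screening section supplies the threshold, with the reference that the outcome sentence also cites: "Scores greater than or equal to 10 on the PHQ-9 are indicative of major depression [48". A score of 10 or more is required at the telephone screen and again at the visit: "Patients who score greater than or equal to 10 at this second PHQ screening appointment will then be invited to complete baseline assessments". On the other side of the line: "Patients who score less than or equal to 9 at this second screening appointment will be informed that they do not meet".

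The PHQ-9 score appears in three further places. The Analysis section uses it as a covariate: "controlling for the following baseline covariates: patient age, gender, ethnicity, and baseline PHQ-9 score". The economic sensitivity analysis (end of the Health economics analysis section) uses its severity as an alternative outcome: "the outcome measure used in the ICER including 1) severity of depressive symptoms (SCL-90, PHQ-9". Table 2 schedules the PHQ-9 at screening, baseline and 6 months.

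**The concern.** If the diagnosis is defined at 10 or more, selection has fixed the starting state. Everyone is a case at the second screen, so change can run only from case to non-case. Patients admitted at 10, 11 or 12 need lose only one to three points to be counted as no longer depressed, and some will do so through measurement error alone. A fall from 20 to 11 counts for nothing.

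Two things are at stake. The proportion who lose the diagnosis would look like recovery although part of it is noise. And the PHQ-9, the only other depression scale in the outcome set and so the natural check on the SCL-90 result, would be less able to confirm or contradict that result than the collected data allow. The screening section also says that 10 was chosen partly to take in sub-threshold distress, which makes a score of 9 hard to describe as a changed diagnosis.

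**Working it through.** **Inputs from the protocol (Sample size).** 15 practices per arm, 15 patients each, 20% attrition, ICC 0.06, 5% level (two-sided assumed), standardised effect 0.4: "we have powered this trial to detect a standardized effect size of 0.4".

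**Reproducing the stated power.**
- Patients per practice after attrition: 15 × 0.8 = 12; per arm 15 × 12 = 180.
- Design effect: 1 + (12 − 1) × 0.06 = 1.66.
- Effective n per arm: 180 / 1.66 = 108.4.
- Noncentrality: 0.4 × √(108.4 / 2) = 2.945.
- Noncentral t with 30 − 2 = 28 df gives 81.1%, against the stated 81.2%. The normal approximation, Φ(2.945 − 1.96), gives 83.8%.

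The stated figure fits a continuous outcome, which the SCL-90 scale is. The comparison below uses the normal approximation on both sides.

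**Noise crossing the cut-off.** The model is three measurements of an unchanged trait, X = μ + σ(√r·T + √(1 − r)·e), with T and the three errors e independent standard normal and X rounded to whole points. Patients are selected if the first two values are 10 or more, and the share below 10 on the third is counted. Reliability r, mean μ and SD σ are assumptions; the protocol gives none of them.
- r = 0.70, μ = 6, σ = 5: 27% (highest).
- r = 0.85, μ = 9, σ = 6: 11% (lowest).
- Among those scoring 10 to 12 at the second screen, 23% to 37% across the same range.

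**Power of the dichotomy.** Assume that d = 0.4 and ICC 0.06 hold for a normally distributed PHQ-9 score, and that a proportion p of controls scores below 10 at 6 months. The protocol does not give p; 0.3 to 0.7 is the assumed range.
- Intervention proportion: p₂ = Φ(Φ⁻¹(p) + 0.4).
- Cutting a clustered normal score lowers its ICC. With c = Φ⁻¹(p), the binary ICC is [Φ₂(c, c; 0.06) − p²] / [p(1 − p)], where Φ₂ is the bivariate normal distribution function. This gives about 0.03 to 0.04.
- Example, p = 0.5: p₂ = 0.655; binary ICCs 0.038 and 0.036; effective n 180 / (1 + 11 × 0.0382) = 126.7 and 180 / (1 + 11 × 0.0362) = 128.7. The standard error is √(0.5 × 0.5 / 126.7 + 0.655 × 0.345 / 128.7) = 0.061. The ratio is 0.155 / 0.061 = 2.546, and power is Φ(2.546 − 1.96) = 72%.
- Relative efficiency in the example: (2.546 / 2.945)² = 0.75.

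| Controls below 10 | Intervention below 10 | Power, dichotomy | Relative efficiency |
|---|---|---|---|
| 30% | 45% | 71% | 0.73 |
| 40% | 56% | 73% | 0.75 |
| 50% | 66% | 72% | 0.75 |
| 60% | 74% | 70% | 0.71 |
| 70% | 82% | 66% | 0.64 |

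Power on the score is 84% under the same assumptions. Between about 24% and 36% of the information is lost.

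**The case against.** Several objections have force.

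The outcome sentence states no cut-off, and the screening section also mentions 12 as a more conservative threshold. So 10 is an inference. It is a strong one: the reference is shared, and 12 is discussed but not adopted.

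The Analysis section speaks of depression outcomes in the plural and fits a linear mixed model with baseline PHQ-9 score as a covariate. That wording can accommodate the PHQ-9 score, and which summaries are tabulated is commonly left to an analysis plan. But the outcome section does say how the PHQ-9 will be used, and it names only the dichotomy. A permissive model description leaves the choice between score and dichotomy open.

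A threshold measure is a reasonable clinical complement to a continuous primary outcome. That also stands, and it is a reason to keep the proportion as description.

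A reader might go further in three ways that the document does not support:
- **That PHQ-9 severity is never used as an outcome.** The economic sensitivity analysis uses it.
- **That regression to the mean biases the comparison.** It acts in both randomised arms. The double screen, added to remove transient depression, also reduces it.
- **That about 35% to 45% of the information is lost.** The textbook loss for splitting a normal score is 36% at an even split and 42% at 30/70. Carrying ICC 0.06 over to the binary outcome likewise gives power of only about 57% to 66%. Both ignore the fall in ICC when a clustered score is cut.

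**Conclusion.** The point holds as an inexpensive improvement to a supporting outcome. Within the effectiveness outcomes the PHQ-9 has only a dichotomous role, and the cut-off is unstated but implied to be the entry criterion. On that reading the outcome is simply a score below 10 at 6 months.

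The noise share of 11% to 27% depends entirely on the assumed reliability, mean and SD. The power gap of 84% against 66% to 73% assumes that the trial's effect size and ICC apply to the PHQ-9 score, that the score is roughly normal, and that 30% to 70% of controls fall below 10. The direction is more secure than the exact figures.

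The consequence is inflated apparent recovery within arms and a weaker contrast between them. The between-arm comparison stays unbiased, and the SCL-90 primary outcome and its power statement are untouched.

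**What to change.** In the Primary outcome section, name the 6-month PHQ-9 score, adjusted for its baseline value in the mixed model of the Analysis section, as the PHQ-9 outcome. State the cut-off for the dichotomy. Keep the proportion scoring below 10 as a descriptive summary by arm, labelled as PHQ-9 below threshold and not as a change of diagnosis. A further composite that combines the threshold with a proportional fall is optional and not needed.

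The cost is a wording change and one more line of analysis. Table 2 already schedules the score at baseline and 6 months. Fixing this before outcome data are compared by arm also removes any later choice between the score and the dichotomy.
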